### Randomization Procedures and Intervention Conditions

#### Randomization Procedures

Stratified permuted block randomization with blocks of sizes 2 and 4 will be used to randomize consenting women into the control arm or the intervention arm in a one-to-one fashion. The stratification will be based on the diabetic status of the woman. The randomization will be done by a statistician who is not involved in recruiting patients. A randomized list was created by the biostatistician, which was later uploaded to Research Electronic Data Capture (REDCap; Vanderbilt University) [18,19], a web-based software package for data management. This allows for the lack of human involvement on the part of the research team in the assignment of a participant to a group. It also allows for the on-the-spot assignment of participants into either the control or intervention groups.

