### Data Collection Procedures and Study Assessments

The RCT includes 2 data collection time points—baseline and 6-month follow-up. We will attempt to collect 6-month assessments for intervention participants regardless of their engagement with the intervention. Participants will receive a remuneration of US $40 after completing each survey. Baseline and follow-up data will be collected and managed using REDCap. Women who do not choose to complete REDCap assessments will be contacted by phone by the research assistant to complete the assessment by phone or in person.

This study’s primary outcomes are a reduction in depressive symptoms, anxiety symptoms, and perceived stress. Secondary outcomes are closely linked with core MB content; secondary outcomes include behavioral activation, social support, mood regulation, decentering of thoughts, and MB skill use. The outcome associated with our exploratory aim is diabetes self-care. All measures have been validated in Arabic.

We will also assess various aspects of intervention implementation. We will conduct client surveys at the end of each MB module to assess clients’ perceptions of intervention acceptability and satisfaction. Each survey lasts 2-3 minutes and asks 3 questions pertaining to enjoyment with MB material, understanding of MB material, and anticipated use of MB material. Six months after a facilitator begins MB delivery with a client, the facilitator will receive a REDCap survey to report on the extent to which they covered all topics within an MB session (on average) and the extent to which clients were engaged in the MB material during intervention sessions.

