### Statistical Analysis

A flowchart will be constructed based on the CONSORT (Consolidated Standards of Reporting Trials) guidance to show the number of recruited, excluded, lost to follow-up, and analyzed participants. Descriptive statistics will be used to summarize baseline characteristics overall and by study arm. As appropriate, mean (SD) and frequency (proportions) will be used to summarize continuous and categorical variables, respectively. Median (IQR) will be used in cases of skewed or nonnormal distributions. Analyses will use normal theory methodology as appropriate, and in cases of violations of assumptions, transformations or nonparametric analyses may be used. We will use SPSS (version 27; IBM Inc) to perform all analyses.

Analyses will be done using the intent-to-treat principle and will compare the 3 primary outcomes between study arms using the independent 2-tailed *t* test (or the Wilcoxon rank sum test in cases where outcomes were highly skewed). The analyses above will be repeated using univariate linear regression to be able to adjust later for any imbalances in baseline characteristics between the study arms and the baseline values of the primary outcomes. Additional analyses will include fitting multivariate linear regression models for each of the 3 main outcomes to assess the effectiveness of the intervention while adjusting for the baseline value of the outcome and any observed imbalances in participants between the 2 study arms. Unadjusted and adjusted mean differences in the primary outcomes between the 2 study arms will be presented along with their standard deviations and *P* values. For the primary outcomes, missing data at 6 months will be imputed using the average of the patients in that group or other methods such as multiple imputation by chained equations, and the primary analyses will be repeated as a sensitivity analysis. Secondary outcomes will be analyzed by comparing study arms using the chi-squared test (or Fisher exact test if expected cell counts are below 5) for categorical outcomes and the independent 2-tailed *t* test (or Wilcoxon rank sum test for highly skewed data) for numeric outcomes. Compliance with the intervention will be assessed by counting the number of intervention sessions received.

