### Power and Sample Size Calculations

With 105 participants recruited per study arm and an estimated attrition of 20%, the study will be able to detect an effect size of 0.5 in any of the 3 primary outcomes using the independent 2-tailed *t* test with a power of 80% and a significance level of .017.

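### The powered primary comparison is unadjusted: adjusting for the baseline score and the diabetes stratum in one named primary model would gain precision at no cost and settle which scale and which result count

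*Protocol article*

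**What the plan says.** All from the Protocol article.

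- **Primary test.** Statistical Analysis will "compare the 3 primary outcomes between study arms using the independent 2-tailed" *t* test, with the Wilcoxon rank sum test as substitute for highly skewed outcomes. The comparison is then repeated as a univariate linear regression.
- **Power.** Power and Sample Size Calculations rests on the same *t* test. It says "the study will be able to detect an effect size of 0.5 in any of the 3 primary outcomes", with "a power of 80% and a significance level of .017", for 105 recruited per arm and 20% attrition.
- **Baseline adjustment.** This is listed under additional analyses, as regression models "adjusting for the baseline value of the outcome and any observed imbalances in participants between the 2 study arms". Unadjusted and adjusted differences are both to be presented with P values.
- **Outcome scale.** Data Collection Procedures and Study Assessments says the "primary outcomes are a reduction in depressive symptoms, anxiety symptoms, and perceived stress", and the hypothesis in the Introduction is also worded as greater reductions. Statistical Analysis does not say whether the tested variable is the 6-month score or the change from baseline.
- **Stratum.** Randomization Procedures says "The stratification will be based on the diabetic status of the woman". No model in Statistical Analysis names diabetic status.

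**The concern.** Assessments take place at baseline and 6 months, and diabetic status is known at randomisation. Everything needed for a baseline-adjusted primary analysis is therefore in hand, yet the powered comparison is unadjusted. Three things follow.

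1. Precision is given up. In a randomised comparison, adjusting for the baseline value of the outcome removes the part of the follow-up variance that baseline explains.
2. Covariates in the adjusted model are chosen by looking at the trial's own data. The adjusted estimate is then not fully specified in advance, while the one covariate that the design singles out, the stratum, is left to chance.
3. Two choices stay open: whether the *t* test is applied to 6-month or change scores, and which result carries the conclusion if the unadjusted and adjusted analyses fall on opposite sides of .017.

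**Working it through.** **Inputs.** 105 per arm, 20% attrition, effect size 0.5, two-sided alpha .017 and 80% power, all from Power and Sample Size Calculations. Evaluable per arm: 105 × 0.8 = 84. The baseline to 6-month correlation *r* is not in the article; it is assumed, and a range is shown.

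**Step 1. The plan's own figure.**
- Normal approximation: n per arm = 2(2.387 + 0.842)² / 0.5² = 83.4, so 84. 84 / 0.8 = 105. This matches exactly.
- Power at 84 per arm: 80.3% by the normal approximation, 79.6% by the noncentral *t*. The noncentral *t* needs 85 per arm for 80%, a trivial difference.

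**Step 2. Baseline adjustment, with 0.5 in SD units of the 6-month score.** The residual variance is multiplied by 1 − *r*², so the effective effect size is 0.5 / √(1 − *r*²). Noncentral *t*, 84 per arm, alpha .017:

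| Assumed *r* | Effective effect size | Power, adjusted | Power, *t* test on 6-month score |
|---|---|---|---|
| 0.2 | 0.510 | 81.4% | 79.6% |
| 0.3 | 0.524 | 83.7% | 79.6% |
| 0.5 | 0.577 | 90.7% | 79.6% |
| 0.7 | 0.700 | 98.3% | 79.6% |

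At *r* = 0.5, 80% power would need 64 evaluable per arm instead of 85.

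**Step 3. Baseline adjustment, with 0.5 in SD units of the change score.** The *t* test on change then has 79.6% power whatever *r* is. With equal SDs at both times, the change SD is √(2(1 − *r*)) in 6-month SD units. The effective effect size under adjustment is 0.5 × √(2(1 − *r*)) / √(1 − *r*²) = 0.5 × √(2 / (1 + *r*)).
- *r* = 0.3: 0.620, power 94.5%
- *r* = 0.5: 0.577, power 90.7%
- *r* = 0.7: 0.542, power 86.4%

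Under either reading of the effect size, adjustment is at least as good at every *r* shown.

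**Step 4. Cost of leaving the choice open.** Suppose an analyst reported the smaller P of the 6-month *t* test and the adjusted model. Under no effect, the two test statistics have correlation of about √(1 − *r*²). The chance that at least one exceeds the two-sided .017 limit (±2.387) is .0225 at *r* = 0.3, .0260 at 0.5 and .0278 at 0.6, so roughly .023 to .028. Simulation at 84 per arm agrees (.022 at *r* = 0.3, .026 at 0.5).

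**Step 5. What adjustment does to the scale question.** In a linear regression that includes the baseline value, using the 6-month score or the change as the response gives the same arm coefficient and P value, up to the sign convention. The adjusted model therefore removes the ambiguity.

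**The case against.** The case on the other side is substantial, and most of it stands.

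- An unadjusted *t* test in a randomised trial is valid. Ignoring the stratum usually makes it slightly conservative. The sample size reproduces, so nothing falls short of the plan's own target.
- The gain depends on an *r* that the article does not give. Entry is restricted to EPDS or GAD-7 ranges (or a past history of major depression), which may lower *r*. At 0.3 the gain is only about 4 points.
- A journal article may leave model detail to an analysis plan that is not shown. But the article does state the primary test, the place of the adjusted models and the imbalance rule, and those are what this point addresses.

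Three stronger readings are tempting, but the article does not support them.

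1. *The primary test is a change-score test and is underpowered.* The word reduction may only give the expected direction. Statistical Analysis speaks of missing data at 6 months and of baseline values to be adjusted for, which fits the 6-month score at least as well. A power loss on change scores also requires 0.5 to be in 6-month SD units, which the article does not say, and it depends on the SDs at the two times. If the baseline SD were half the 6-month SD, the change variance at *r* = 0.3 would be 1 + 0.25 − 2 × 0.3 × 0.5 = 0.95 of the 6-month variance, and power would be about 82%.
2. *Each outcome has several rival primary results.* The *t* test comes first and is the only test powered. The adjusted models are labelled additional, and the imputed repeats are a sensitivity analysis. The univariate regression on arm merely reproduces the equal-variance *t* test.
3. *The plan's error rate is inflated.* Taking the smaller P is nowhere specified, and presenting both estimates together limits selective reporting. Step 4 describes possible misuse, not the stated procedure.

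**Conclusion.** The point holds as a free improvement and should be fixed; it is not a fault that invalidates the design. The primary comparison omits the baseline adjustment and the stratum, the adjusted model takes covariates from observed imbalance, and the article leaves open both the tested scale and the result that prevails.

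The precision given up is about 2 points of power at *r* = 0.2, 4 at 0.3, 11 at 0.5 and 19 at 0.7 if 0.5 is in 6-month SD units. If it is in change-score SD units, with equal SDs, the loss is about 15 points at *r* = 0.3 and 7 at 0.7. These sizes rest on the assumed *r*, 84 evaluable per arm and a linear relation to baseline. The further effect of including the stratum cannot be computed from the article.

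**What to change.** Name one primary analysis for each of the three outcomes: a linear regression of the 6-month score on arm, the baseline value of that outcome and diabetic status, tested at .017. State that this result carries the conclusion.

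- List any further covariates before outcome data are seen, and delete observed imbalance as a selection rule.
- Keep the *t* and Wilcoxon tests as supportive analyses.
- State in which SD units the effect size of 0.5 is expressed.
- Use the same model for numeric secondary outcomes measured at baseline.

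The cost is analysis wording only. The variables are already collected, regression in SPSS is already planned, and the sample size need not change. The article reports 157 of 210 enrolled by 31 March 2023, with recruitment still open. The change should be dated and made before outcomes are compared by arm.

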**Methods:**

A multidisciplinary and multiethnic investigator team adapted MB to promote cultural and contextual fit for Arabic-speaking women. Intervention concepts were reviewed to ensure core content would be understood by Arabic-speaking women in Qatar. Subsequently, images, activities, and examples in the intervention manuals were adapted, as needed, to make the content more relevant to Arab culture. To deliver the adapted intervention, 30 Arabic-speaking individuals with mental health backgrounds were trained. The adapted intervention was subsequently pilot-tested with 10 pregnant women receiving prenatal care at Sidra Hospital in Doha. We are now conducting an RCT to examine the effectiveness of the adapted intervention. We plan to enroll 210 pregnant individuals who are Arabic-speaking, with 1:1 randomization to the MB intervention or usual prenatal care. Among the enrolled participants, a stratified subsample of 40 pregnant women with diabetes is being recruited. Data collection will take place at baseline and a 6-month follow-up. The primary outcomes are depressive and anxiety symptoms and perceived stress. Diabetes self-care is the exploratory outcome for the subsample of individuals with diabetes. Intervention implementation will be assessed via client and provider surveys during and after intervention delivery. Power and sample size were calculated using a 2-sided 5% effort rate and assumed analyses on the individual level, accounting for attrition of 20%.

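### The primary between-arm mean differences are to be shown with standard deviations, which either do not express their precision or mislabel the standard error

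*Protocol article*

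**What the plan says.** The Statistical Analysis section of the protocol article compares the three primary outcomes (depressive symptoms, anxiety symptoms, perceived stress) between arms by a two-sample t test, or by a Wilcoxon rank sum test if an outcome is highly skewed. Linear regression follows, first unadjusted, then adjusted for the baseline value and for observed imbalances. The same section then fixes how the results are shown: the between-arm differences in means, both before and after adjustment, "will be presented along with their standard deviations", together with P values.

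Earlier in that section, SD has its ordinary descriptive meaning: "mean (SD) and frequency (proportions) will be used to summarize continuous and categorical variables". The article mentions neither a standard error nor a confidence interval.

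The Power and Sample Size Calculations section sets "a power of 80% and a significance level of .017" for 105 women recruited per arm with 20% attrition.

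**The concern.** A between-arm mean difference is an estimate. Its uncertainty is given by its standard error or, better, a confidence interval. A standard deviation of scores measures how much women differ from one another and does not shrink as the trial grows. Because the section has already used SD in that descriptive sense, a reader will naturally carry the meaning over to the treatment effects. The adjusted difference is a regression coefficient, and a coefficient has no standard deviation other than its standard error.

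The trial describes itself as the first of its kind in the Middle East and is sized for a standardised effect of 0.5. If a primary comparison is not significant, what matters is which effects remain plausible. An interval shows that directly; an SD and a P value do not. Anyone pooling the result who took the printed figure for a standard error, when it was an outcome SD, would give the trial far too little weight.

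**Working it through.** **Inputs.** From Power and Sample Size Calculations: 105 recruited per arm, 20% attrition, effect size 0.5 (taken as a standardised difference), power 80%, significance level .017, two-sided test. Allocation is 1:1 (Randomization Procedures). The article gives no outcome SD, so SD is set to 1 and all results are in SD units.

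**1. The plan's own sample size.**
- Evaluable per arm = 2 × (z for .017 two-sided + z for 80% power)² / 0.5² = 2 × (2.387 + 0.842)² / 0.25 = 83.4, rounded up to 84.
- Recruited per arm = 84 / 0.80 = 105. This reproduces the stated figure.
- Power at 84 per arm is 80.3% by the normal approximation and 79.6% by the noncentral t distribution.

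None of this depends on the reporting sentence.

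**2. Standard error of the unadjusted difference.**
- SE = SD × √(2/n).
- At 84 per arm: √(2/84) = 0.154 SD. Ratio of outcome SD to SE = 1/0.1543 = 6.5.
- At 105 per arm (no attrition): √(2/105) = 0.138 SD. Ratio = 7.2.

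The ratio holds whatever the common SD is.

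**3. Interval half-widths at 84 per arm (t distribution, 166 degrees of freedom).**
- 95%: 1.974 × 0.1543 = 0.305 SD.
- 98.3% (that is, 1 − .017): 2.411 × 0.1543 = 0.372 SD.

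**4. The two readings, for an observed difference of 0.5 SD.** The test gives t = 0.5/0.1543 = 3.24, P = 0.0014.

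| What is printed beside 0.5 | Value | What follows |
|---|---|---|
| Standard error, labelled SD | 0.154 | Right number, wrong name |
| Outcome SD | 1 | If taken as an SE: 0.5 ± 1.96 × 1 = −1.46 to 2.46 |
| 95% confidence interval | 0.20 to 0.80 | Precision shown directly |
| 98.3% confidence interval | 0.13 to 0.87 | Precision shown at the trial's own test level |

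**5. Can the standard error be rebuilt?** For the unadjusted difference, yes: arm SDs and arm sizes give it by step 2. For the adjusted difference, outcome SDs do not suffice, because its SE depends on the residual SD after adjustment and on how the covariates relate to arm. An exact regression P value together with the estimate would give it, but the sentence does not promise exact P values. Where the Wilcoxon test replaces the t test, its P value does not come from the mean difference and cannot be converted in this way.

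**The case against.** The strongest defence is grammatical: the standard deviations belong to the differences, and the standard deviation of an estimated difference is its standard error. Regression output normally gives a standard error beside each coefficient, so that may well be what would be tabulated. On this view the number is right and only the label is loose. This is a fair reading and cannot be excluded. It still leaves the sentence ambiguous between two quantities that differ about 6.5-fold, in a section that uses SD descriptively elsewhere.

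A reader might infer that the published uncertainty of every treatment effect will be wrong. The article does not support that. The figure may be a mislabelled standard error; if it is an outcome SD, it is a valid descriptive statistic that misleads only when taken as a measure of precision. The P values come from the tests and the regression and are unaffected.

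A reader might also infer that no confidence interval is planned for any effect. That cannot be established either. The sentence covers the primary outcomes only, and the article condenses a fuller protocol and analysis plan that are not shown and may specify intervals. The point rests on what the published sentence states, not on what it leaves out.

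It is also true that an approximate interval can often be reconstructed from an estimate and an exact P value. This softens the consequence, within the limits in step 5 of the working.

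**Conclusion.** The point holds as a reporting defect. For its primary results the article names a statistic that either does not measure the precision of the difference or is the standard error under another name. Under the first reading the printed figure is about 6.5 times the standard error at 84 evaluable per arm (7.2 times at 105), and the precision of the adjusted difference cannot be obtained from it.

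The tests, the significance level, the power and the sample size all stand, and the stated 105 per arm reproduces. The figures assume equal arms, a common SD and 20% attrition. The half-widths apply to the unadjusted difference; the precision of the adjusted one depends on covariate correlations that the article does not give.

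**What to change.** Reword the sentence so that each unadjusted and adjusted mean difference in the three primary outcomes is presented with its confidence interval and P value, and so that SDs are given only for the score summaries of each arm. State the interval level: 95%, or 98.3% to agree with the .017 level used for sizing. One stated level is enough. If the full analysis plan already specifies intervals, bring the article's sentence into line with it.

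The cost is one sentence. Nothing changes in recruitment, data collection, testing or sample size. The article expected recruitment to run to December 2023, so on that timetable the change could be made before the final analysis; it can still be applied when the results are written up.

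### The plan permits missing 6-month outcomes to be filled with the arm average; if that option is used, the sensitivity t test cannot detect an effect of dropout and its standard error is about 20% too small at the planned attrition

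*Protocol article*

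**What the plan says.** Under Statistical Analysis, the protocol article compares the three primary outcomes between arms with an unadjusted two-sample t test, or a Wilcoxon rank sum test if an outcome is highly skewed. Linear regressions adjusting for baseline follow. For the primary outcomes, "missing data at 6 months will be imputed using the average of the patients in that group"; the same sentence goes on to allow other methods, with chained-equations multiple imputation as the example. After imputation, "the primary analyses will be repeated as a sensitivity analysis". Nothing says which method will be used or on what ground, and no variance correction is mentioned for the arm-average option.

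Under Power and Sample Size Calculations, the article assumes "an estimated attrition of 20" per cent and "a significance level of .017" for each primary outcome, which is about .05/3.

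**The concern.** Imputation in a sensitivity analysis should show whether the conclusion survives other reasonable assumptions about the women who were not measured, and should carry the extra uncertainty from not having measured them. Arm-average filling does neither. It gives every missing woman the completers' mean in her own arm, so the arm means cannot move. It also treats the filled values as real data, so the SD falls while the sample size rises.

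At stake is how the robustness claim is read. A repeat with an identical difference and a smaller p-value looks like confirmation, although nothing has been tested. A result that misses the .017 threshold in the primary test could pass it in the repeat with no new information.

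**Working it through.** **Inputs (protocol article).**
- Randomised per arm: n = 105 ("With 105 participants recruited per study arm", Power and Sample Size Calculations), allocated 1:1 (Randomization Procedures).
- Attrition 20%, so observed per arm m = 0.80 × 105 = 84.
- Standardised effect 0.5, power 80%, two-sided α = .017 (same section).
- Analysis repeated after imputation: the unadjusted two-sample t test (Statistical Analysis).
- "Group" is read as study arm, the only grouping that fits the context.

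**Step 1. Reproduce the plan's figure.** The number per arm is 2(z₁₋α/₂ + z₀.₈₀)² / 0.5² = 8 × (2.387 + 0.842)² = 83.4, so 84. Allowing for attrition, 84/0.80 = 105. Power with 84 per arm is 0.803 by the normal approximation and 0.796 by the noncentral t. The stated 80% is reproduced.

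**Step 2. Effect on the estimate.** Let x̄ be the observed mean in an arm. After filling, the arm mean is [m·x̄ + (n − m)·x̄]/n = x̄. The difference between arms equals the completers' difference, whatever the cause of dropout.

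**Step 3. Effect on the standard error.** The filled values add no squared deviations, so the variance becomes s²(m − 1)/(n − 1), and it is then divided by n instead of m. Taking SD = 1:
- Observed data: SE = √(2/84) = 0.154.
- Arm-average filled: SE = √(83/104) × √(2/105) = 0.893 × 0.138 = 0.123.
- Ratio = √[(83/104) × (84/105)] = 0.799.

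The SE is about 20% too small and the t statistic grows by 1/0.799 = 1.25. For example, an observed-data t of 2.00 (p = .047, not significant at .017) becomes 2.50 (p = .013, significant).

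**Step 4. Type I error of the repeated test.** The filled-data test uses 2 × 105 − 2 = 208 df, with critical value 2.406 at α = .017. In terms of the observed-data t (2 × 84 − 2 = 166 df), it rejects when |t| > 0.799 × 2.406 = 1.923. That probability is 0.056. At a nominal .05 it is 0.117. A simulation of 200,000 trials gave 0.056 and 0.117.

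**Step 5. Range by attrition** (equal in both arms, nominal .017):

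| Attrition | Observed per arm | SE too small by | Type I error |
|---|---|---|---|
| 10% | 94 | 10.5% | 0.033 |
| 15% | 89 | 15.3% | 0.043 |
| 20% | 84 | 20.1% | 0.056 |
| 25% | 79 | 24.9% | 0.073 |
| 30% | 74 | 29.7% | 0.093 |

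**Step 6. If the baseline-adjusted regression is repeated instead.** With an assumed baseline–outcome correlation of 0.5 and 4,000 simulated trials per setting, the estimate shifts slightly. The SE is about 18% smaller than with observed data and type I error is about 0.06. This holds with 84 observed in each arm and with 75 and 93.

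**The case against.** The strongest reply is that the same sentence names a sound alternative. A reader might infer that the planned sensitivity analysis is invalid outright. The text does not support that: if chained-equations imputation is used, none of the figures above apply. The final imputation model may also be left to an analysis plan that is not shown. What stands is that the article itself lists an unsound method first and would be fully complied with by using it alone.

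A reader might also take 5.6% as the trial's type I error. It is not. Imputation is confined to the sensitivity repeat; the primary t test, its .017 level and the power calculation are untouched, and the primary p-value would still be reported.

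Nor is this analysis the trial's only protection against attrition. The article provides for tracking information at recruitment, follow-up regardless of engagement, assessment by phone or in person for women who do not complete the online form, weekly reports on missing data and retention, and a sample size inflated for loss. It also plans baseline-adjusted models, which can reduce bias where dropout depends on baseline scores. It is fair to say only that imputation is the one sensitivity analysis for missing outcomes that the article names.

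Finally, exact agreement with the completers holds for the unadjusted mean difference. It is only approximate for the adjusted regression, and the SE and type I figures do not carry over to the Wilcoxon test.

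**Conclusion.** The point holds as a defect in a permitted option. If the arm average is used, the repeated t test returns the completers' difference unchanged and overstates its precision: at the planned attrition the SE is 0.80 of its proper value and the test's type I error is about 5.6% instead of 1.7%. That puts the per-outcome error of this repeat above .05, although the .017 level appears to be set for three outcomes.

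The figures assume 20% loss in each arm, roughly normal outcomes with equal variance, dropout unrelated to outcome (for the type I error) and the unadjusted t test. The SE comparison is with the valid observed-data test; against a hypothetical complete sample of 105 per arm the SE would be about 11% too small (√(83/104) = 0.893).

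Because the defect is avoidable, sits in a supportive analysis and leaves the primary inference intact, it should be fixed but does not undermine the trial.

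**What to change.** Delete the arm-average option. State that missing 6-month primary outcomes will be imputed in the sensitivity analysis by the multiple imputation by chained equations already named, with study arm, the baseline score of the outcome and the diabetes stratum in the imputation model, and with results pooled by Rubin's rules.

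A delta-adjusted analysis, in which imputed scores are shifted to represent outcomes missing not at random, would be a useful but optional addition.

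The cost is a one-sentence change and slightly more analysis work, with no new data and no change to trial conduct. Sensitivity p-values will be less favourable than under arm-average filling, because they will reflect the information actually collected.
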